### Statistics

#### Sample size calculation

With a true prevalence of [1; 2; 5; 1%; 2%; 5%] and an expected sample size of *n* = 2500 participants, a precision of the estimate of [±1; ±2; ±3; ±4; ±5; ±9] (i.e., the width of a 95% confidence interval) is to be achieved, which is considered sufficient. Note, on April 9th, 2021, SARS-CoV-2 prevalence of confirmed cases in Cologne was 3.9% [20].

#### Analysis

The distributions of the collected data will be first described with the usual parameters of location and distribution, i.e. mean, standard deviation, percentiles (0., 25., 50., 75., 100.) for continuous variables, absolute and relative frequencies for qualitative variables.

Associations and correlations will be described by means of contingency tables and regression methods (e.g. logistic regression for dichotomous target variables). With regard to the prevalence of SARS-CoV-2, the following variables are of particular interest: age, gender, neighbourhoods, housing size, number of household members, pre-existing conditions, previous positive testing, potentially contagious contacts. Where possible, important statistical measures will be provided with 95% confidence intervals to indicate the precision of the estimate.

Due to the expected limited participation rate (we estimate 40%) studies of the representativeness of the sample obtained are of particular importance. On the basis of the information provided by the non-participants, an extrapolation to the Cologne population will be carried out. (Notabene: The risk of non-participation due to lack of reading and language skills should be minimized by the assistance of native speakers. Otherwise, a bias correction will be attempted as described below.) Official statistics on the total population of Cologne are available at https://www.stadt-koeln.de/politik-und-verwaltung/statistik/ (accessed 22.01.2021). Sensitivity analyses examine the correction for various bias constellations. For this purpose, corresponding weights will be used in combination with regression methods.

The calculations will be performed using scripts for the programming languages R (R Foundation for Statistical Computing, Vienna, Austria), SAS (SAS Institute Corp., Cary, NC, USA), Stata (StataCorp LLC, College Station, TX, USA) and SPSS Statistics (IBM Corp., Armonk, NY, USA).

### Data management

An instance of the Internet application REDCap (Research Electronic Data Capture) (Vanderbilt University, Nashville, TN, USA) hosted at the Clinical Trials Center Cologne will be used to record the questionnaires. A single MySQL database will store all of REDCap’s data and associated system and project information. This open source relational database management system makes use of foreign keys and indexes to accommodate the project and system data.

## Discussion

Despite the importance of surveillance for the current SARS-CoV-2 pandemic, specific data on prevalence and incidence of SARS-CoV-2, the association between risk of infection and demographic factors, as well as behavioural factors, are still scarce in Germany. This information can be used to identify risk factors for infections, better understand how the virus spreads and evaluate the efficacy and efficiency of public health measures. A cohort study can provide these data. The rolling cohort in Cologne will provide a representative sample.

The CoCoS study presents a self-sampling strategy as a surveillance strategy. This approach allows us to reach a large and representative sample of Cologne citizens and it is less labour-intensive than taking samples from mobile testing sites [23] or general practitioners [24]. It is crucial that response rates are high using self-sampling, as low participation rates negatively affect the generalizability of results. With support from the Cologne authorities and a media announcement, we are hopeful that 40% of the 6000 residents invited for participation will respond.

Our self-sampling method of choice was saliva swab, which is particularly easy to handle for participants, and is comparable to the gold standard in the diagnosis of acute infections with SARS-CoV-2, nasopharyngeal swab [25].

The Cologne Corona Surveillance Study will consider several factors to ensure that responses do not correlate with acute infections. A self-sampling design will allow residents who have acute symptoms or who are under quarantine to participate in the study. In order to ensure representativeness of the study results, self-sampling and questionnaires can be completed at home and are time-free. This allows residents who are unable to visit a test centre during regular working hours (e.g. working hours) to participate.

One-week response time should ensure comparability of epidemiological background. A simple study description with step-by-step instructions was used, as well as an accessible phone number for assistance with self-sampling kits and questionnaires to reach residents with as wide a range of experiences as possible.

Nevertheless, our study is not without limitations. We cannot rule out the possibility that people with little computer experience or no Internet access might be less likely to complete the questionnaire. This is particularly relevant in the case of older residents. It is possible that older participants may not be able to provide consent to participate in our study or may struggle with the administrative challenges to participate. Therefore, the representativeness of data from older participants in our study must be critically analysed. In addition, foreign-born residents who do not speak German as their first language may have difficulties understanding the invitation letter and refrain from participating in the study. Further, our study does not include residents under 18 years of age and will not detect SARS-CoV-2 positive individuals currently in intensive care.

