### Study procedures

Figure 1 shows the surveillance strategy that is planned to be implemented. The 6000 randomly selected Cologne citizens will be notified by regular mail, with all envelopes being sent out simultaneously. Besides the invitation letter, a saliva sample and a pre-addressed, stamped UN3373 envelope will be included in the package. Participants will be required to give written informed consent and to send a saliva sample within 1 week of receiving the package to the Institute of Virology, University Hospital Cologne. On the informed consent form, participants will record the exact date of the saliva sampling.

At the University Hospital of Cologne, the existence of a written informed consent will be checked, saliva samples will be analysed and participants who test positive will be notified immediately. Participants will also be provided with a QR-code and a link for completing the study questionnaire online, as well as a phone number to call study staff in case they need assistance. Participants can choose to complete the questionnaire during a telephone interview with a member of the study team. All participants are asked to inform study staff if they experience symptoms between testing rounds. A second testing round will take place 6 weeks after the first. Data on non-participation will be collected along with demographic and socioeconomic information of non-responders, as well as reasons for non-participation. In order to assess representativeness, the data will be compared with official statistics of the City of Cologne.

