### Study instruments

#### Questionnaires

The first round of the CoCoS study survey will be conducted using a standard questionnaire that includes questions about personal data, such as age and health status, risk behaviours, and potential sources of infection. Therefore, we can detect possible sources of infection, as well as assess socioeconomic factors in our participants. We also hope to explore potential correlations between infection status and socioeconomic factors.

The CoCoS questionnaire is aligned with the ELISA and MuSPAD questionnaires developed by the ‘Helmholtz Zentrum für Infektionsforschung’ [22]. The questionnaire was then adjusted for the specific focus of the CoCoS study, consisting of five starting questions, plus 23 main questions in the first round and 17 questions in the second round, to which follow-up questions were added based on the selected answers. Several sections are included in the questionnaire, including personal information, housing conditions, household members, education and employment, possible symptoms, past SARS-CoV-2 test results, preventive behaviours and possible sources of infection. The CoCoS questionnaire is estimated to take from 5 to 10 min to complete.

Participants will be asked to fill out their specific ID at the beginning of each interview in order to ensure that only our study members can access the questionnaire and to be able to match their sample to the interview.

The second round of the questionnaire will examine issues that may have changed from round one to round two.

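### Home sampling cannot ensure that response is unrelated to infection; the plan should show prevalence over a range of infection-dependent response ratios and name this bias as a limitation

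*Protocol article*

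**What the plan says.** The Discussion states that several factors will be considered "to ensure that responses do not correlate with acute infections". Two design features support this. One is that "A self-sampling design will allow residents who have acute symptoms or who are under quarantine to participate in the study". The other is that sampling and questionnaire are done at home without a fixed hour, which helps people who cannot reach a test centre while at work.

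Study procedures says that "a saliva sample and a pre-addressed, stamped UN3373 envelope will be included in the package" and that "participants who test positive will be notified immediately". For people who do not respond, the same section lists demographic and socioeconomic information and their reasons for not taking part, and it plans a comparison with official city statistics.

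The Analysis section expects 40% participation and announces: "On the basis of the information provided by the non-participants, an extrapolation to the Cologne population will be carried out". It adds sensitivity analyses for several unnamed bias scenarios, using weights together with regression. The weighting variables are not named.

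The participants' questionnaire covers "possible symptoms, past SARS-CoV-2 test results, preventive behaviours and possible sources of infection". The limitations at the end of the Discussion address internet access, older residents, language, minors and patients in intensive care. They do not mention response that depends on suspected or known infection.

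**The concern.** Letting symptomatic and quarantined residents take part removes a barrier. It does not settle whether they are more or less likely to do so. A kit sent to the home, with notice of a positive result, may draw in people with symptoms or a recent contact. People who are ill, or who already know they are positive, may see little reason to take part. The net direction is unknown.

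Aim 1 is to estimate prevalence and the extent of undetected infection. At low prevalence the observed proportion scales almost one-for-one with the ratio of response in infected to uninfected residents. If response depends on infection within age, sex or social strata, weighting on those strata leaves the bias in place, and the confidence interval describes only sampling error. A reader who accepts the Discussion's statement would take the interval as the full uncertainty.

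**Working it through.** **Inputs.** From the documents: 6,000 invited, 40% response expected (Analysis; Discussion), hence 0.40 × 6,000 = 2,400 participants; prevalences of 1%, 2% and 5% and a 95% interval (Sample size calculation); 3.9% confirmed in Cologne on 9 April 2021 (same section). Assumed: the response ratio r of infected to uninfected residents, examined from 0.5 to 2.0.

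**The plan's own precision.** Half-width = 1.96 × √(p(1−p)/n). With the section's n = 2,500 this gives 0.39, 0.55 and 0.85 points at 1%, 2% and 5%. These agree with the printed 4, 5 and 9 read as tenths of a point, the decimals having apparently been lost in the text. With n = 2,400 the half-widths are 0.40, 0.56 and 0.87 points.

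**Bias.** If infected residents respond r times as often as uninfected residents, the expected observed prevalence is p·r / (p·r + 1 − p).

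| True p | r = 0.5 | r = 0.8 | r = 1.25 | r = 1.5 | r = 2 |
|---|---|---|---|---|---|
| 1% | 0.50% | 0.80% | 1.25% | 1.49% | 1.98% |
| 2% | 1.01% | 1.61% | 2.49% | 2.97% | 3.92% |
| 5% | 2.56% | 4.04% | 6.17% | 7.32% | 9.52% |

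**Ratio at which bias equals the half-width (n = 2,400).** Put q = p ± half-width and solve r = q(1−p) / (p(1−q)).

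- p = 1%: q = 1.398%, r = (0.01398 × 0.99)/(0.01 × 0.98602) = 1.40; downwards, r = 0.60.
- p = 2%: q = 2.560%, r = 1.29; downwards, 0.72.
- p = 5%: q = 5.872%, r = 1.19; downwards, 0.82.

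A ratio of 1.40 means, for example, 56% response among infected against 40% among uninfected residents.

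**Coverage.** At true 2% and n = 2,400, exact binomial summation gives coverage of the nominal 95% Wald interval of 94% at r = 1, 70% at r = 1.25, 18% at r = 1.5, 62% at r = 0.8 and 1% at r = 0.5.

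**Does demographic weighting help?** Take three assumed strata with population shares 30/45/25%, prevalence 3/2/1% and response among the uninfected of 30/40/50%. True prevalence is 0.30 × 3 + 0.45 × 2 + 0.25 × 1 = 2.05%. At r = 1, weighting to the strata corrects the crude 1.91% to 2.05%. At r = 1.5 the crude value is 2.84% and the weighted value 3.04%. Weighting repairs the difference between strata and leaves the infection-dependent part within them.

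**A diagnostic in the planned data.** Participants report past test results. At 3.9% ever confirmed, 0.039 × 2,400 ≈ 94 are expected, with a margin of 1.96 × √(0.039 × 0.961/2,400) = 0.77 points. If the ever-confirmed responded at a ratio of 0.75 or 1.3, the expected share would be 2.95% or 5.01%, and the overall comparison would flag it with probability 0.69 or 0.78. In assumed age groups of 800 these fall to about 0.25 and 0.38, so only the overall comparison is useful.

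**The case against.** Four points can be made for the plan.

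- **The sentence may express an aim.** It says factors will be considered, and the abstract says openly that representativeness is unclear. That softens the claim. It does not remove it, because the features cited still concern access only and the limitations leave this bias out.
- **The correction is wider than demographics.** A reader might infer that the plan corrects on demographics alone, that the bias would go undetected, or that every bias scenario is tied to demographic weights. The documents do not support this. Socioeconomic data and reasons for not taking part are also collected, and the reasons could give a partial signal. The scenarios and weighting variables are unnamed, so infection-dependent ones are not excluded. What stands is narrower: no listed non-responder item concerns symptoms, contacts, earlier tests or infection.
- **Scenario detail may belong in an analysis plan that is not shown.** That is fair as to the full list. It does not cover a statement in this article that the problem is dealt with by design.
- **The benchmark is imperfect.** Ever-confirmed residents may stay away while those who suspect infection come forward, so calibrating weights to earlier confirmed infection could worsen the estimate of current prevalence. The official figure is not exact either. Setting gives 38,565 cases in about 1.1 million residents, or 3.5%, against 3.9% in the sample size section, and neither is restricted to adults. This objection stands in full and rules out using the benchmark as a weighting margin.

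That the test is an incentive is also an inference: the text states the supplied kit, the postage and notification of positives, nothing more.

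**Conclusion.** The statement in the Discussion claims more than the design can deliver. Home sampling and flexible timing may reduce the dependence of response on infection; they cannot exclude it. Weights on the listed non-responder information would not remove what remains within strata. With 2,400 participants, a ratio of about 1.40, 1.29 or 1.19 (true prevalence 1%, 2%, 5%) moves the estimate by the whole 95% half-width, and ratios of 0.60, 0.72 or 0.82 do so downwards.

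These sizes rest on assumed ratios. The documents do not show that such a ratio will occur or which direction it would take, so the finding is about unstated uncertainty and is not a prediction of bias. It should be dealt with because it bears on Aim 1 and the remedy is cheap.

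**What to change.** 1. **Analysis section.** Name infection-dependent response as one of the bias scenarios, and report prevalence over a fixed grid of response ratios (for example 0.5 to 2.0) beside the main estimate. For observed prevalence o the corrected value is o / (o + r(1−o)). An observed 2% becomes 3.92% at r = 0.5 and 1.01% at r = 2.
2. **Analysis section.** Compare the overall share of participants reporting an earlier confirmed infection with the official cumulative confirmed share of Cologne adults at the sampling date. Use it as a diagnostic only, not as a weighting margin, and state that it is a proxy for response by the currently infected.
3. **Discussion.** Replace *ensure* with *reduce the chance*, and add response that depends on suspected or known infection to the limitations.

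The cost is a little extra analysis on data already planned, plus an official count restricted to adults. The drawback is that the reported range of plausible prevalence becomes wider.

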## Data Availability

Not applicable.

## Abbreviations

CoCoS-study: Cologne Corona Surveillance Study
SARS-CoV-2: Severe Acute Respiratory Syndrome-Coronavirus-2
PCR: Polymerase Chain Reaction
DRKS: German Clinical Trials Register
COVID-19: Corona Virus Disease 19
RT-qPCR: Quantitative reverse transcription PCR
RNA: Ribonucleic Acid
